### Non-participant observation of care

Structured non-participant observations of the experience of care on the MMHU and standard care wards are undertaken using Dementia Care Mapping [22]. For this we include a randomly selected sub-sample of 44 patient participants from the MMHU and 44 patient participants from standard care wards. Patients in the two settings will therefore be matched for disease severity and other factors. Observations are made every five minutes for four to six hours at a time. Field notes are made, and semi-quantified mood and engagement scores, activity codes, and quality of staff interactions with patients are completed.

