#### Sequence generation

The randomisation sequence is generated using a computer random number generator, in a 1:1 ratio, and a permuted block design with varying block sizes up to 6, stratified by prior care home residence.

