#### Allocation concealment

The randomisation sequence is concealed from clinical staff who use the computer to allocate patients. However, research staff collecting baseline data are not blind to treatment allocation.

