#### Descriptive statistics, univariate and multivariate analyses

Baseline and outcome data for each treatment group will be presented as follows: continuous data that are approximately normally distributed will be summarised in terms of the number of observations, mean, standard deviation, minimum and maximum. Skewed data will be transformed to normality, if possible, or otherwise presented in terms of the number of observations, median, lower and upper quartiles, minimum, and maximum. Categorical data will be summarised as frequency counts and percentages.

We will compare baseline differences between groups descriptively to explore whether there are differences in the characteristics of those recruited in the MMHU and standard care groups. The design of this study, with recruitment following randomisation, means that baseline differences may occur that have not arisen by chance, and we will therefore also carry out statistical significance testing of differences at baseline, using parametric or non-parametric tests, as appropriate to the distribution of measured variables.

Analyses of primary and secondary outcomes will be by intention to treat including all those recruited, and will compare differences between MMHU and standard care:

• Mean/median days at home, and total length of hospital stay (and 95% confidence intervals for the differences)

• Proportions dead, at home, in new care homes and readmitted (and 95% confidence intervals for the differences)

• Mean/median scaled outcomes for patients and carers (and 95% confidence intervals for the differences).

• Quantitative and qualitative analysis of the non-participant observer study.

• Proportions of participants receiving various assessment and interventions recorded in the case notes (and difference in proportions with 95% confidence intervals).

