## Discussion

### Justification for design

The study design had to accommodate the constraints of an acute medical service very pressed for bed availability, and under rigorous performance management of patient flows, in particular, the government-prescribed maximum four hour Emergency Department wait target. This stipulates that all patients must be assessed, treated, and discharged or transferred from Emergency Departments (ED) within four hours of arrival. This, in turn, puts pressure on Acute Medical Admissions Units, who must have empty beds to accept transfers from ED, and on wards to have capacity to accept patients from Admission Units.

It was, therefore, unacceptable to the clinical service for potential trial participants to remain on the Acute Medical Admissions Unit whilst awaiting research assessment or recruitment procedures, or for there to be more than three empty beds on the MMHU. It had to be possible to admit to the MMHU 24 hours a day and seven days a week, regardless of researcher availability, and to keep the ward full with appropriate patients. Proper time for consultation, consent or consultee agreement for research participation to be given, is necessary for legal and ethical reasons. The consultation and consent process takes longer than the clinical processes for swift bed management. So it was impossible to run a conventional randomised controlled trial with recruitment prior to allocation: clinically patients had to be allocated before they could be recruited.

Previous work demonstrated that 30% of acute medical patients over 65 had cognitive impairment, far more than could be accommodated on a single ward. Some allocation mechanism was therefore required by the clinical service. In usual clinical practice, ward allocation is largely driven by bed availability, but in this case the service agreed to allocate suitable patients at random, either to the MMHU, or standard care on another general or geriatric medical ward.

The allocation algorithm ensures that the MMHU remains acceptably full, without compromising recruitment to the trial. Only patients who have been randomly allocated, and their carers, are invited to participate in the trial.

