### Implications of design

Strictly, the design violates best practice for a randomised controlled trial, since only randomised patients who consent, or have consultee agreement, can be followed up. For this reason, we have chosen to describe it as a 'controlled clinical trial'. However, it approximates to a pragmatic, parallel group, randomised controlled trial.

The main scientific concern about the design is failure to recruit a patient after randomisation. This introduces the potential for bias (for example, if it proves easier to recruit from one setting than the other). Baseline data cannot legally or ethically be collected for research purposes from randomised patients who do not consent (or have consultee agreement) to take part.

Despite the risk of differential recruitment bias, an important consideration is that this design enables us to undertake a trial at all. A conventional randomised controlled design would either have failed because of conflict with the demands of the clinical service, or would have recruited an unrepresentative population. If we attempted to recruit with inadequate consent or consultation, the trial would be illegal, and would be open to bias through high withdrawal rates.

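### The observation sub-study calls its 44 + 44 patients matched for severity, but random sampling of patients recruited after allocation does not match them; correct the claim and adjust the comparison for baseline severity

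*Protocol article*

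**What the plan says.** The protocol article, under Non-participant observation of care, draws "a randomly selected sub-sample of 44 patient participants from the MMHU and 44 patient participants from standard care wards" and infers from this: "Patients in the two settings will therefore be matched for disease severity and other factors". It describes no matching variables and no matching procedure.

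Other sections describe where these participants come from:

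- Justification for design: "clinically patients had to be allocated before they could be recruited".
- Allocation concealment: "research staff collecting baseline data are not blind to treatment allocation".
- Sequence generation: randomisation is "stratified by prior care home residence". No measure of severity is a stratification factor.
- Descriptive statistics, univariate and multivariate analyses: because recruitment follows randomisation, "baseline differences may occur that have not arisen by chance".
- Implications of design: failure to recruit a randomised patient is named as the chief scientific worry, with easier recruitment in one setting as the example.

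On analysis, the list of comparisons in the data analysis section gives only a quantitative and qualitative analysis for the observer study. A general clause after that list provides for regression with adjustment, as appropriate, for apparent baseline differences and prognostic variables. Additional measures to avoid bias says that the baseline data will make adjustment possible.

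**The concern.** The word 'therefore' rests matching on random selection alone. Random selection makes each group of 44 representative of the recruits in its own setting. It does nothing to make the two sets of recruits alike. If recruitment differed by setting, the sub-sample inherits the difference.

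Better quality of care and patient experience on the Unit is one of the secondary hypotheses, and the sub-study is meant to help show whether and how care differs. Mood and engagement scores plausibly depend on how severe a patient's dementia or delirium is, although the article does not say so. If they do, a difference in patient severity could be read as a difference in care. An analyst who takes the groups as matched has no reason to adjust.

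**Working it through.** The article gives no sample size or power calculation for 44 + 44, so there is no stated figure to reproduce. The check is mainly one of logic. The arithmetic only illustrates size.

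**1. What random sampling delivers.** Let δ be the difference in mean severity, in SD units, between all recruits on the Unit and all recruits on standard wards. The expected difference between random sub-samples of 44 is also δ. It is zero only if recruitment after allocation was unrelated to severity, or related to it equally in both settings. The protocol says that this cannot be assumed. Its matching sentence therefore conflicts with its own statements on baseline differences and on recruitment bias.

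**2. Chance imbalance (δ = 0).** The standard error of a standardised baseline difference is √(1/n + 1/n).

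- n = 44: √(2/44) = 0.213; 95% range ±1.96 × 0.213 = ±0.42 SD.
- n = 300 (the whole trial): √(2/300) = 0.082; 95% range ±0.16 SD.

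Even with perfect randomisation, then, the 88 are not matched in the ordinary sense. This variation is already reflected in the standard error and confidence interval of the comparison. It concerns precision and is not confounding.

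**3. Systematic imbalance (δ ≠ 0).** The bias in an unadjusted comparison is ρ × δ, where ρ is the correlation of severity with the observed score. The true type I error of a nominal 5% test is 1 − Φ(1.96 − b) + Φ(−1.96 − b), with b = ρδ/0.213. The documents give neither ρ nor δ; both are assumed here.

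| δ (SD) | Bias, ρ = 0.3 | Type I error | Bias, ρ = 0.5 | Type I error |
|---|---|---|---|---|
| 0.1 | 0.03 | 5.2% | 0.05 | 5.6% |
| 0.2 | 0.06 | 5.9% | 0.10 | 7.6% |
| 0.3 | 0.09 | 7.1% | 0.15 | 10.8% |
| 0.5 | 0.15 | 10.8% | 0.25 | 21.6% |

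Example: ρ = 0.5 and δ = 0.3 give a bias of 0.15 SD and b = 0.15/0.213 = 0.70. At δ = 0.1 the effect is minor.

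**4. Would baseline tests show the shift?** The power of a two-sided 5% test for δ = 0.1, 0.2 and 0.3 is 7%, 15% and 29% at 44 per group. At 300 per group it is 23%, 69% and 96%. Testing within the 88 is thus a poor way to decide whether to adjust, or for what.

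**The case against.** The case against is substantial.

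- **No unadjusted analysis is planned.** The general regression clause can be read to cover the observer study, and the severity measures are already in the baseline list. A reader might infer from the matching claim that the protocol has chosen an unadjusted comparison. The text does not say so, and a condensed article may leave the covariate list to a fuller document. This stands.
- **The recruitment bias is disclosed.** The authors state it openly and monitor the proportion recruited by setting. On a charitable reading, the sentence means only that groups sampled from randomised patients should be comparable on average. But comparability on average still depends on unbiased recruitment, and 'matched' claims more than that.
- **Chance imbalance is not bias.** A reader might treat the ±0.42 SD as evidence of confounding. It would apply to any randomised comparison of 44 with 44, and the confidence interval allows for it.
- **Selection by length of stay.** A reader might infer that only longer-staying patients can be observed, and that the Unit may change length of stay. The section does not say when in the stay patients are sampled or observed, so this is conjecture.
- **Limited reach.** Observation measures are not among the listed primary or secondary outcomes, and the hypothesis is worded as an association in an observational study. The primary outcome is untouched.

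What remains is a false statement about the design that bears on a stated hypothesis, together with an inexpensive safeguard that the false statement makes look unnecessary.

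**Conclusion.** The concern holds in a limited form. The two groups of 44 are random samples of patients recruited after allocation. They are not matched for severity, and they are comparable only as far as recruitment was unbiased. The claim contradicts what the same article says about its own design. It should be corrected, and the observer comparison should be protected by adjustment.

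The documents do not establish that a biased analysis is planned, or that any bias is large. Its size rests on two assumed quantities. Across a shift of 0.1 to 0.5 SD and a correlation of 0.3 to 0.5, the bias in an unadjusted difference runs from 0.03 to 0.25 SD, and the type I error from about 5% to 22%. The lower end is negligible.

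**What to change.** 1. Replace the matching claim with a statement that the patients are randomly sampled from recruited participants and so are comparable only as far as recruitment was unbiased.
2. Tabulate the baseline characteristics of the 88 observed patients by setting.
3. Make the main quantitative observer comparison a regression adjusted for a short list fixed in advance from data already collected: MMSE, Delirium Rating Scale, Barthel index and care home residence. Do not choose the covariates by baseline significance tests.
4. Optionally, report the day of stay on which each patient was observed.

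The cost is a wording change, one table and a simple regression on data already held. Four covariates entered as single terms use four degrees of freedom in 88 patients. Adjustment deals only with the measured factors and cannot remove recruitment differences in unmeasured ones, so the revised wording is needed as well as the model.

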### Recording of health care interventions

Ninety days after randomisation we scrutinise medical, nursing and therapy case notes to ascertain 139 items of assessment, investigation, treatment, information-giving and future care planning information.

Together with the non-participant observer study this will help define if, and how, care delivered in the two settings differs.

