#### Medical and Mental Health Unit

The MMHU was developed over 18 months prior to trial commencement. The unit was previously a 28-bedded acute geriatric medical ward. We have described the development and philosophy of the ward elsewhere [8]. In brief, we enhanced five componants:

• Specialist mental health staff additional to the normal ward complement of medical, nursing and therapy staff, comprising three registered mental health nurses, a specialist mental health occupational therapist (OT), 0.5 whole time equivalent (WTE) specialist physiotherapist, 0.2 WTE speech and langauge therapist, 0.2 WTE additional geriatrician time and 0.1 WTE psychiatrist time, and four unregistered health care assistants, two of whom took on the role of activities co-ordinators. New documentation was introduced for mental health assessments and OT interventions.

• Training for all staff in the philosophy of person-centred dementia care. This emphasises respect for the person with dementia as an individual with a history, values and preferences, and the right to make choices. Confrontation is avoided, and activity and diversion promoted, based on making meaningful connections with the person with dementia's retained abilities.

• A programme of therapeutic and leisure activites was instituted to try to maintain abilities, prevent distress behaviours, and promote night-time rest. Patients are got up and dressed if not too ill.

• The environment was made more appropriate. The ward had to relocate after nine months of development, to one which was longer and with better lay out, when it was realised that sufficient adjustments could not be made in the original one. Noise (such as from radios and equipment alarms) is minimised. Orientation cues, appropriate signage and some safety modifications were made. Bed spaces are personalised.

• A proactive and inclusive approach to family carergivers is promoted, with active communcation, involvement in decision making, and inclusion in hands on care, if willing.

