#### Trial documents

The documents to be completed, and by whom, are recorded in table 1.

**Table 1 T1:** Trial documentation

Form title	Completed by
Screening log (computerised)	MMHU ward nurses

Capacity assessment form	Researcher

Patient participant information and consent forms	Patient with capacity to consent

Consultee information and agreement forms	Family member of carer (on behalf of patient without capacity to consent)

Carer participant information and consent forms	Family member or carer

Professional information and agreement forms	Nurse in charge of ward (on behalf of patient without capacity to consent and with no contactable carer)

Identifiable data form	Researcher

Patient participant initial data form	Researcher

Carer initial data form	Family member or carer/researcher

Medical data form (from casenotes)	Researcher

Dementia care mapping raw data sheets	Researcher

Patient participant follow-up data form	Researcher

Carer follow-up data form	Family member or carer/researcher

Resource use from computerised records	Health economist

Health care intervention form	Medically qualified researcher

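### For mental health assessment and OT items, the case-note comparison may mix extra care on the MMHU with more complete recording, because the MMHU package included new documentation in those domains

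*Protocol article*

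**What the plan says.** Three statements in the protocol article bear on this.

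- *Medical and Mental Health Unit* lists the components that were enhanced. In the item on additional specialist staff it says: "New documentation was introduced for mental health assessments and OT interventions".
- *Recording of health care interventions* says that researchers will "scrutinise medical, nursing and therapy case notes to ascertain 139 items of assessment, investigation, treatment, information-giving and future care planning information". It gives the purpose: "Together with the non-participant observer study this will help define if, and how, care delivered in the two settings differs".
- *Descriptive statistics, univariate and multivariate analyses* lists the comparison as "Proportions of participants receiving various assessment and interventions recorded in the case notes", with differences in proportions and 95% confidence intervals.

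The sections on treatment definition, *Standard care* and *Contamination* mention no new forms on other wards. The observer study named alongside the case-note work uses Dementia Care Mapping in a "randomly selected sub-sample of 44 patient participants from the MMHU and 44 patient participants from standard care wards".

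**The concern.** The case notes are the measuring instrument for care delivered, and in two domains the intervention appears to have changed that instrument in one arm. A standard-ward patient who was assessed without an entry being made counts as not having received the item. An MMHU patient given the same assessment may have a form that prompts the entry. The analysis wording then treats a record as receipt.

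The article describes the treatment as a black-box package, and this is one of two sources meant to show whether and how the packages differed. If the process difference on these items is partly a recording difference, two readings become unsafe. A null primary result could be explained as better care that did not work, and a positive one could be credited to items whose excess is partly on paper. Mental health assessment and OT are also the domains where added MMHU staff make a real difference most likely, so real and recorded effects are hardest to separate there.

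**Working it through.** **No figure to reproduce.** The article states no expected proportion, recording rate or power for the case-note comparison. Its 80% power statement concerns days at home.

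**What the comparison estimates.** Let p1 and p0 be the true proportions receiving an item on the MMHU and on standard wards, and s1 and s0 the probabilities that a delivered item is recorded. Assume that undelivered items are not recorded. The recorded difference is

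p1·s1 − p0·s0 = (p1 − p0)·s0 + p1·(s1 − s0).

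The first term is real extra care, shrunk by incomplete recording. The second is a pure recording effect. Only the sum is observed. If s1 = s0 the second term vanishes. If p1 = p0 = p the whole difference is the artefact p·(s1 − s0).

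**Inputs.** 300 per arm comes from *Power and sample size*. This assumes that notes are read for all participants. Every value of p and s is assumed. The test is two-sided at 5%, also assumed, since the article specifies only 95% intervals.

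**Results with identical care (p1 = p0)**

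| True receipt | Recording, standard v MMHU | Recorded, standard v MMHU | False difference (points) | Chance of p < 0.05 |
|---|---|---|---|---|
| any | equal | equal | 0 | 5% |
| 30% | 80% v 85% | 24% v 25.5% | 1.5 | 6% |
| 50% | 80% v 90% | 40% v 45% | 5 | 24% |
| 50% | 70% v 90% | 35% v 45% | 10 | 71% |
| 70% | 70% v 90% | 49% v 63% | 14 | 93% |
| 50% | 60% v 90% | 30% v 45% | 15 | 97% |

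A second set of assumptions takes 60% true receipt and 95% recording on the MMHU, so the recorded proportion there is 0.60 × 0.95 = 57%. The z value is the difference divided by √[(a(1−a) + b(1−b))/300], where a and b are the two recorded proportions.

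| Recording on standard wards | Recorded, standard v MMHU | False difference (points) | z | Two-sided p |
|---|---|---|---|---|
| 85% | 51% v 57% | 6 | 1.48 | 0.14 |
| 75% | 45% v 57% | 12 | 2.96 | 0.003 |
| 65% | 39% v 57% | 18 | 4.49 | < 0.0001 |

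With unequal recording, these scenarios run from 1.5 to 18 points. Neither end is a bound: equal recording gives zero, and 70% receipt with 60% v 90% recording gives 0.70 × 0.30 = 21.

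**Whether anything in the plan removes the recording term**

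- Baseline adjustment does not. It addresses differences between patients, and this is a difference in how care is written down.
- Dementia Care Mapping does not depend on ward records. However, it covers 44 participants per setting and scores mood, engagement, activity and staff interactions over four to six hours at a time. It cannot verify most mental health assessment or OT items.
- The blinding statement in *Ascertainment of outcomes* concerns outcome assessments. The health care intervention form is listed separately in Table 1, with no blinding stated. Even blind extraction would not recover care that was never recorded.

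**The case against.** The strongest reply is that this is a caveat on a supporting measure. Several parts of that reply stand.

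- **Scope.** The new documentation is described for mental health assessments and OT interventions only. The 139 items also cover investigation, treatment, information-giving and future care planning. A reader might infer that the whole case-note comparison is invalid. The article does not support that, and without the item list the number of affected items cannot be given.
- **Certainty.** A reader might infer that the MMHU is bound to look better even if care were identical. That requires poorer recording of delivered care on standard wards, which the article neither states nor quantifies. The artefact could be negligible.
- **MMHU-only use.** This is inferred from where the sentence sits. It is the natural reading, but the article does not describe ward documentation elsewhere.
- **Real effects of forms.** A structured form can prompt real assessment, and specialist staff were added at the same time. Part of any excess is plausibly genuine.
- **Consequences.** Case-note items are not among the primary or secondary outcomes, and the quality-of-care hypothesis is tied to the observational study. The notes are only said to help define differences, and no mediation analysis is planned.
- **Level of detail.** Item-by-item classification could properly sit in a fuller document, so its absence from the article is not itself a fault.

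It is also fair that the analysis line says the items are recorded in the notes. That discloses the source, but the quantity reported is still the proportion receiving care. The article itself fixes the source, the inference to delivered care and that wording, and the point rests on these.

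**Conclusion.** The concern holds for the case-note items on mental health assessment and OT intervention, and is not shown beyond them. For those items a recorded excess on the MMHU cannot be read simply as more care received, because it may combine extra care with fuller recording. The likely direction favours the MMHU. The size is unknown: the range of about 1.5 to 18 points rests wholly on assumed receipt and recording rates, with identical care and 300 per arm.

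A reader might call this confounding. It is differential ascertainment, which baseline adjustment cannot remove. The conclusion also assumes that the new documentation was not used on standard wards; if it was, the problem largely disappears. The primary and secondary outcomes are not shown to be affected. What changes is how far the trial can say that delivered care differed in these two domains.

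**What to change.** 1. Before any between-arm comparison, classify the 139 items into those captured by an MMHU-specific form and those recorded on documents common to all wards. Confirm at the same time which wards used the new forms.
2. Report the two sets separately.
3. In *Descriptive statistics, univariate and multivariate analyses*, replace *receiving* with *with a record of*.
4. Claim a difference in delivered care on the form-affected items only with the recording change stated as an alternative explanation. Use the commonly recorded items and the observer study as the less biased evidence.

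The form-affected items should not be dropped, because they cover the domains where the MMHU is most expected to act.

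The cost is one classification of an existing list and a wording change, with no new data. The downside is that fewer items give unqualified support for a care difference, and the result may look less favourable to the MMHU.
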